#### Other Secondary Outcomes

Other secondary outcomes include (1) the proportion of eligible patients in whom all applicable primary quality indicators are achieved (not all quality indicators are applicable in every patient) and the association of this composite outcome with early recurrence rate and (2) the rate of complications of grade 3 or greater, within 30 days of surgery according to the Clavien-Dindo [42] classification.

### Sample Size

The intervention will be delivered to centers, and so the primary outcomes will also be measured at the center level. The only published data about intersite achievement of the listed coprimary outcomes are the Scottish Quality Performance Indicator programme covering 11 sites in Scotland. The outcome with the largest SD (SI-IVC) was used to determine the overall sample size. With mean 0.651 (SD 0.2) for SI-IVC, recruiting 172 sites (86 per arm) would give 90% power to detect a difference of 0.1 between the intervention and control groups at the 5% significance level. Where a smaller SD of 0.1 (detrusor muscle in specimen) or 0.15 (resection documenting) can be assumed, this would provide 90% power at the 5% significance level to detect differences of 0.05 and 0.075, respectively. It is possible that some sites may have missing data for 1 or more of the coprimary outcomes. Missing data will not be imputed for the primary outcomes. In that case, the site will be excluded from the analysis for that outcome. A sensitivity analysis will be performed to determine the effect of missing data in that outcome. An extensive international marketing campaign will be undertaken to ensure sample size is reached, along with endorsement of the study by the British Association of Urological Surgeons to all urology centers in the United Kingdom.

### Analysis

The average rate of achievement of each of the 4 co-primary outcomes per site will be compared between sites that received education and feedback and those that did not. The primary outcomes will be analyzed using mixed effects linear regression to compare the outcome between the group that received audit, feedback, and education and the control group. The primary outcomes are the proportion of cases where the relevant outcome is obtained and measured at the site level (a continuous variable). The regression model will have fixed effects for the study arm (intervention group); audit already in place at the site before the study; and the baseline achievement of the relevant outcome. A random effect will be included for the region. Outcomes will be assessed in subgroups of low- and high-grade tumors, tumors with estimated maximum diameter of ≤3 cm or >3 cm and in single vs multiple tumors for the detrusor muscle, and intravesical chemotherapy outcomes.

The early recurrence rate is a secondary outcome. This is measured at the patient level. In this instance, the outcome is binary. A mixed effect logistic regression will be used including random effects for site and surgeon to incorporate the 2 levels of clustering. Fixed effects will be included for intervention arm and tumor variables known to be associated with early recurrence (tumor size, tumor number, grade, and stage). Patient age will also be included as a fixed effect. A second analysis will be undertaken for the early recurrence outcome at the patient level to determine if the quality indicators are associated with reduced recurrence rate regardless of performance feedback.

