#### Randomization

Sites will be randomized 1:1 in parallel arms when the submission of the minimum required retrospective data is complete. Sites will be randomized to either (1) no intervention (the site continues to submit data on consecutive eligible cases but without performance feedback and education during the study). Once the study is complete, these sites will be provided with performance and education feedback or (2) audit, feedback, and education (performance feedback and education provided before beginning further prospective phase of study).

Sites will be randomized using the randomization app at the Centre for Healthcare Randomised Trials (CHaRT), University of Aberdeen, which developed the randomization sequence. This randomization app is available 24 hours a day, 7 days a week as a web-based app. Randomization will be minimized for site-level variables that are thought to significantly impact achievement of TURBT quality indicators. There is no blocking. These are baseline performance from the baseline audit, geographical region (continent, except that the United Kingdom is considered alone, Australia will be combined with mainland Europe), and the presence of an existing TURBT audit at that site before the study. In addition, a random component is used in the minimization algorithm to ensure concealment of the allocation.

The study administrator will access the web-based system. They will enter the minimization variables into the web-based system, which returns the allocation status. The chief investigator of the site will be informed of their allocation following randomization. There is no blinding. To prevent contamination following randomization, sites randomized to no intervention will not be granted access to the dedicated personalized feedback and education resources, which are username and password protected.

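### The early recurrence model leaves out the three factors used to balance sites, which costs some precision and makes the test conservative, without biasing the comparison

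*Protocol article*

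**What the plan says.** The protocol article allocates whole sites: "Sites will be randomized 1:1 in parallel arms when the submission of the minimum required retrospective data is complete". On the balancing factors, its Randomization section states: "Randomization will be minimized for site-level variables that are thought to significantly impact achievement of TURBT quality indicators". It then names them: "These are baseline performance from the baseline audit, geographical region (continent, except that the United Kingdom is considered alone", and finally "the presence of an existing TURBT audit at that site before the study".

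The Analysis section specifies two models in consecutive paragraphs. Besides study arm, the primary model has fixed effects for "audit already in place at the site before the study; and the baseline achievement of the relevant outcome", and on geography it says "A random effect will be included for the region". For early recurrence the section says "A mixed effect logistic regression will be used including random effects for site and surgeon to incorporate the 2 levels of clustering", then "Fixed effects will be included for intervention arm and tumor variables known to be associated with early recurrence", naming size, number, grade and stage. Patient age completes the list.

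The recurrence paragraph has no term for region, existing audit or any site baseline. Secondary Analyses lists region and a pre-existing audit among factors to be examined for association with the indicators and with recurrence. It does not bring them into the randomised comparison.

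**The concern.** When allocation is balanced on a factor, the arms are more alike on it than simple randomisation would make them. A model that leaves the factor out does not credit that balance: the factor's contribution stays in the between-site variance and enters the standard error of the arm effect. If the factor predicts the outcome, the reported standard error exceeds the real sampling variability and the test rejects too seldom.

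This matters more for recurrence than for most secondary outcomes. It is the key secondary outcome, the Discussion promises an answer on it, and the Sample Size section gives power only for the coprimary outcomes. The section headed The Problem also describes differences between sites in early recurrence that patient, tumor and treatment characteristics do not explain. Yet the recurrence model's only covariates besides arm are tumor characteristics and age, while the site-level variables already held for the minimisation go unused.

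**Working it through.** **Step 1: the two models side by side.**

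| Minimisation factor | Primary model | Recurrence model |
|---|---|---|
| Existing audit | fixed effect | absent |
| Region | random effect | absent |
| Baseline performance | baseline achievement of the outcome analysed | absent |

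The third row is a near match rather than an identity. The article does not define the baseline performance measure used in the minimisation, so it may differ from the outcome-specific baseline in the primary model.

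**Step 2: the plan's own figure.** For SD 0.2, difference 0.1, 90% power and two-sided 5%, the normal approximation gives 2 × (1.960 + 1.282)² × (0.2/0.1)² = 84.1, so 85 per arm. The noncentral t calculation gives 86 per arm, or 172 sites, as stated. This figure is not in dispute; it supplies the number of sites below.

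**Step 3: approximate effect on the standard error.** The article gives no recurrence rate, intracluster correlation or evaluable cases per site for recurrence, so every other input is an assumption. Let τ be the between-site SD on the logit scale, m the evaluable cases per site, p the recurrence rate, and R² the share of τ² that the three factors explain. Then

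SE(log OR) ≈ √{4 × [τ²(1 − R²) + 1/(m p(1 − p))] / 172}.

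Example with p = 0.10, m = 35, τ = 0.5: 1/(35 × 0.09) = 0.317.
- Factors omitted: √(4 × 0.567/172) = 0.115.
- Factors included, R² = 0.5: √(4 × 0.442/172) = 0.101, which is 12% smaller.
- Power at an odds ratio of 0.75 is 0.71 without the factors, and 0.73, 0.76 and 0.81 with them for R² = 0.1, 0.25 and 0.5.

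Over p of 0.10 and 0.20, m of 20 to 70 and τ of 0.3 to 0.8, including the factors shrinks the standard error by about 1–5% (R² = 0.1), 2–12% (R² = 0.25) or 4–25% (R² = 0.5).

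**Step 4: simulation under minimisation.** 172 sites; p = 0.15, m = 35, τ = 0.5; 1,500 runs per setting. Sites were minimised on a five-level region, audit (30% of sites) and dichotomised baseline, with probability 0.8 of the better-balancing arm. The analysis was a linear model on site empirical logits, without tumor covariates or surgeon effects.

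| R² | Type I error, omitted / included | Factors omitted, no effect: mean reported SE / actual SD of estimate | Power at OR 0.75, omitted / included |
|---|---|---|---|
| 0.1 | 0.048 / 0.053 | 0.1086 / 0.1077 | 0.72 / 0.73 |
| 0.3 | 0.037 / 0.052 | 0.1088 / 0.1034 | 0.73 / 0.78 |
| 0.5 | 0.029 / 0.053 | 0.1088 / 0.1006 | 0.74 / 0.82 |

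Without the factors, the reported SE overstates the true variability by about 1%, 5% and 8% (0.1086/0.1077, 0.1088/0.1034, 0.1088/0.1006). The Monte Carlo standard error of a type I error near 0.05 is √(0.05 × 0.95/1500) = 0.006. The included-factor results are therefore compatible with 0.05, and the first row shows no clear loss.

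**Step 5: a separate quantity, the site's own baseline recurrence rate.** This is not a minimisation factor. With between-site SD s on the proportion scale, m₀ baseline cases, m₁ prospective cases and stable site effects,

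r = s² / √{[s² + p(1 − p)/m₀] × [s² + p(1 − p)/m₁]},

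and adjustment removes about r² of the site-level variance. With p = 0.2:
- s = 0.08, m₀ = 30, m₁ = 40: r = 0.0064/√(0.01173 × 0.0104) = 0.579, r² = 34%.
- The same, with site effects correlated 0.7 between periods: 0.336 × 0.49 = 16%.
- s = 0.08, m₀ = 20 (the site minimum), m₁ = 40: 27%.
- s = 0.05, m₀ = 30, m₁ = 40: 12%.
- s = 0.05, m₀ = m₁ = 20: r = 0.0025/0.0105 = 0.238, r² = 6%.

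**The case against.** The strongest reply is that the factors were chosen for their expected link with the quality indicators, not with recurrence. Region and prior audit appear in Secondary Analyses only as variables whose association with recurrence is to be examined. If they explain about a tenth of the between-site variance, power moves from 0.72 to 0.73 and little is lost. This stands, and it limits the size of the point: nothing in the document supports an R² of 0.3 or 0.5 over 0.1.

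A second reply is that this is a condensed article and that its covariate list is not declared complete. This carries less weight. The recurrence covariates are named one by one, next to a primary model that does carry the balancing factors, and no reason is given for the difference.

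Three stronger readings are tempting, and the document does not support them.
- A reader might infer that recurrence is not analysed as randomised. Nothing in the Analysis section moves a site out of its allocated arm, and the site random effect respects the unit of randomisation.
- A reader might infer that the p values are invalid in the sense of false positives. The simulated type I error without the factors lies at or below nominal, so the error is on the conservative side.
- A reader might take the 34% in Step 5 as the cost of omitting the minimisation factors. It concerns a different variable, assumes perfectly stable site effects and 30 and 40 evaluable cases, and ignores the tumor adjustment already in the model. Evaluable counts will also fall below case counts, because recurrence eligibility requires a timely cystoscopy. Nor does the article say explicitly that recurrence is recorded for the retrospective cohort.

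**Conclusion.** The point holds as a modest, avoidable loss of precision in the key secondary comparison. The recurrence model as listed omits all three balancing factors, although the primary model adjusts for audit, region and a site baseline. The consequence is a somewhat inflated standard error and a conservative test, not bias.

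Under the simulation's assumptions, type I error is about 0.03 to 0.05 instead of 0.05, and the power given up at an odds ratio of 0.75 is 1, 5 or 8 percentage points when the factors explain 10%, 30% or 50% of between-site variance. These figures rest on an assumed recurrence rate, number of cases per site, between-site SD and R², and on a simplified site-level analysis. The true loss may be close to nil. The omission merits correction because the fix is nearly free, not because the comparison is unsound without it.

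**What to change.** Before the outcome data are analysed, add region, existing audit and the site baseline performance measure used in the minimisation to the early recurrence model. Region can enter in the same form as in the primary model. Define that baseline measure, since the article does not. If the factors are left out on purpose, state why.

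Separately, and only if recurrence was recorded for the retrospective cases, add each site's baseline early recurrence rate. Its possible gain, roughly 6% to 34% of site-level variance under the assumptions above, should be reported as its own item and not as the price of omitting the balancing factors.

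The cost is a change of wording and a few degrees of freedom out of 172 planned sites. The three minimisation variables are already held, because they are entered when each site is randomised, so no new data are needed for the main change.

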#### Other Objectives

The other objectives are to determine (1) if audit, feedback, and education improves the early recurrence rate of NMIBC after first TURBT; (2) if achievement of TURBT quality indicators is associated with early recurrence rate of NMIBC after the first TURBT; (3) the average and variation in achievement of TURBT surgery quality indicators and early recurrence rate across surgeons, sites, countries, and health care settings (site type and operating list type); and (4) associations among site, surgeon, and surgical factors and achievement of TURBT quality indicators and early recurrence rate.

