#### Quality Performance Indicator 1: The Proportion of Eligible Cases Where Detrusor Muscle Is Present in the Surgical Specimen

##### Rationale

International evidence-based guidelines include clear recommendations related to TURBT [5,7]. There is evidence that resection of detrusor muscle at the index TURBT is associated with reduced early recurrence rate [6,22] and long-term mortality [25] and is more likely to be resected by experienced than inexperienced surgeons [6,22]. If detrusor muscle is not obtained, it is not possible to accurately determine the tumor stage and all of the tumor may not have been removed, which may lead to recurrence. It is accepted that detrusor muscle resection is not appropriate in all patients and is a clinical judgment. Therefore, the average rate of detrusor muscle will be used as a performance indicator.

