##### Eligibility

All cases where the tumor maximal diameter is estimated at >5 mm by the operating surgeon.

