#### Quality Performance Indicator 2: The Proportion of Eligible Cases Where SI-IVC Is Administered Within 24 Hours of TURBT

##### Rationale

There is high-certainty evidence supporting the use of SI-IVC, such as Mitomycin C following TURBT. It is known that SI-IVC administration can significantly reduce the rate of NMIBC recurrence [23,35-39]. EAU and AUA guidelines recommend administration of SI-IVC within 24 hours of surgery in patients most likely to benefit [5,7].

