### Secondary Outcomes

#### Key Secondary Outcome: Early Recurrence Rate

##### Rationale

International guidelines recommend that a “check” cystoscopy be performed approximately 3 months after complete TURBT [5,7]. The rationale is that recurrence detected at this early stage is due to surgical failure rather than disease process [6]. Therefore, the early recurrence rate represents an outcome of surgical quality.

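### The planned analysis of quality indicators and early recurrence does not separate case selection from site or surgeon performance for detrusor muscle and, in part, for SI-IVC

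*Protocol article*

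**What the plan says.** Objective 2 (Other Objectives) asks "if achievement of TURBT quality indicators is associated with early recurrence rate of NMIBC after the first TURBT". The Analysis section assigns this to a second recurrence model: "A second analysis will be undertaken for the early recurrence outcome at the patient level to determine if the quality indicators are associated". The link of interest is to fewer recurrences, whether or not a site had feedback. Other Secondary Outcomes adds an association between recurrence and a composite that is defined for each patient.

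The Rationale for Quality Performance Indicator 1 states: "It is accepted that detrusor muscle resection is not appropriate in all patients and is a clinical judgment". It continues: "Therefore, the average rate of detrusor muscle will be used as a performance indicator". The only case-level filter for that indicator, apart from missing data, is tumor size: "All cases where the tumor maximal diameter is estimated at >5 mm by the operating surgeon".

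For SI-IVC, the Rationale for Quality Performance Indicator 2 reports that guidelines "recommend administration of SI-IVC within 24 hours of surgery in patients most likely to benefit". The trial's own denominator is wider: all cases at sites able to give it, less documented allergy and missing data.

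For the first recurrence model, which compares the arms, the Analysis section specifies random effects for site and surgeon and these covariates: "Fixed effects will be included for intervention arm and tumor variables known to be associated with early recurrence (tumor size, tumor number, grade, and stage"), with age added. It does not say whether the second model uses the same terms.

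**The concern.** The protocol averages the detrusor indicator because one case without muscle may reflect a decision about that lesion rather than poor surgery. The primary analysis follows this and uses site proportions. The second recurrence analysis names no rate, so the reason for averaging is not carried into the analysis that answers objective 2.

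A single patient-level coefficient combines two contrasts. One is between patients at the same site with and without the indicator, where selection acts. The other is between sites with high and low achievement, which is the difference that feedback is meant to change. Random intercepts for site and surgeon do not separate them. They assume that indicator achievement is unrelated to the site and surgeon effects, whereas the protocol's premise is that sites differ in quality and so in recurrence: "Therefore, the early recurrence rate represents an outcome of surgical quality".

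At stake is how objective 2 is read. If selection is strong, the coefficient could be near null or point the wrong way although better-performing sites do have less recurrence. The opposite error is also possible.

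**Working it through.** **The plan's own figure.** For SD 0.2, difference 0.1, two-sided 5% and 90% power, the normal approximation gives 2 × (1.960 + 1.282)² × 0.2² / 0.1² ≈ 84.1, so 85 per arm and 170 sites. The protocol states 172 (86 per arm), and power at 86 per arm is 0.906. The figure reproduces, and this point does not affect it. The document gives no figure for the indicator-recurrence analysis.

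**Where a pooled coefficient gets its weight.** This is a linear approximation with one random intercept, for site.
- From Sample Size: SD 0.1 (detrusor muscle); mean 0.651 and SD 0.2 (SI-IVC).
- Assumed: detrusor mean p of 0.75 to 0.85; recurrence ICC of 0.02 to 0.10; m = 20 to 68 cases per site. Twenty is the site entry minimum, and 15,000 records / 220 hospitals ≈ 68.
- Formulas: w = p(1 − p) − SD²; B = SD² + w/m; W = w(m − 1)/m; ψ = 1/(1 + m·ICC/(1 − ICC)); between-site share = ψB/(ψB + W).

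With m = 40 and ICC = 0.05, ψ = 1/(1 + 40 × 0.05/0.95) = 0.322.

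| | w | B | W | Share |
|---|---|---|---|---|
| Detrusor, p = 0.75 | 0.1775 | 0.01444 | 0.17306 | 0.00465/0.17771 = 2.6% |
| SI-IVC, p = 0.651 | 0.1872 | 0.04468 | 0.18252 | 0.01439/0.19691 = 7.3% |

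Over the assumed ranges the share is 0.8 to 9.2% for detrusor muscle and 2.6 to 16.5% for SI-IVC. If the second model had no site effect at all (ψ = 1), the shares at m = 40 would be 0.01444/0.18750 = 7.7% and 0.04468/0.22720 = 19.7%. In each case most of the weight is within site.

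**Whether selection could matter.** An illustrative logistic simulation used 200 sites × 75 cases, a site-rate SD of about 0.11 and 20 replicates per scenario. The chance that muscle was taken depended on a recorded and an unrecorded case feature. The table gives average odds ratios (ORs), all adjusted for the recorded feature. The site-rate OR is for a change from 0 to 1.

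| Unrecorded feature's effect on recurrence | True OR | Patient-level OR | Within-site OR | Site-rate OR |
|---|---|---|---|---|
| None | 1.00 | 1.00 | 0.99 | 1.06 |
| Weaker | 1.00 | 1.13 | 1.14 | 1.09 |
| Stronger | 1.00 | 1.23 | 1.25 | 1.00 |
| None | 0.70 | 0.71 | 0.71 | 0.63 |
| Weaker | 0.70 | 0.77 | 0.77 | 0.72 |
| Stronger | 0.70 | 0.89 | 0.90 | 0.75 |

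The patient-level and within-site results nearly coincide, as the shares predict. If selection runs only through recorded factors, adjustment removes the bias.

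**Limits of the rate term.** Its log OR varied between replicates with an SD of 0.20 to 0.29 in these scenarios. At 0.20, a true OR of 0.70 has rough 95% limits of 0.70 × e^(±0.392), or 0.47 to 1.04. The simulation contained no site-level confounding, so it cannot show that the rate term would be unbiased in practice. Observed rates are also noisy. Detrusor reliability is SD²/B = 0.01/(0.01 + 0.1775/40) = 0.69 at m = 40 and 0.53 at m = 20, so an effect of underlying site performance would be attenuated.

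**The case against.** The strongest reply is that the sentence fixes the level of the outcome, not how the indicators enter. A model with a site rate and a patient deviation is still a patient-level analysis, and exposure coding can be left to a statistical analysis plan. This stands in part: the proposed model fits the sentence and contradicts nothing in the protocol. But the text names no rate as an exposure, the composite is defined per patient, and the protocol's own reason for averaging would be lost under the plain reading.

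A second reply also stands. A reader might infer that detrusor muscle is meaningful only as an average, so that objective 2 would be answered by clinical judgment instead of surgical performance. The document does not support this. The same Rationale gives a patient-level mechanism, namely that tumor may be left behind when muscle is not obtained, and it cites an association between resection at the index operation and recurrence. The coefficient is a mixture, and adjustment for tumor size, number, grade, stage and age might remove much or all of the selection.

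Third, the argument does not reach resection completeness or tumor-feature documentation, which apply to all cases. It reaches SI-IVC only in part, because selection there is described as guideline practice.

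Finally, the rate coefficient is an ecological comparison, open to differences in case mix, pathology, adjuvant treatment and follow-up. Treating it as the sole answer to objective 2 would exchange one confounding problem for another.

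**Conclusion.** The point holds for detrusor muscle and partly for SI-IVC. As described, the second recurrence analysis does not separate case selection from site or surgeon performance, although the protocol gives case-level judgment as its reason for averaging the detrusor indicator. A pooled coefficient would be almost wholly within-site (between-site share of roughly 1 to 9% for detrusor muscle and 3 to 16% for SI-IVC) and so says little about whether better-performing sites have less recurrence.

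These shares rest on the protocol's SDs, the assumed detrusor mean, ICCs and cluster sizes, and a linear one-level approximation. The direction and size of any selection bias cannot be derived from the document. The patient-level outcome is not itself an error, and neither the primary analysis nor the sample size is affected. This is a worthwhile, low-cost improvement to a secondary analysis.

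**What to change.** In the second recurrence analysis:
- Keep the patient-level binary outcome. State that the tumor covariates, age and the site and surgeon random effects carry over from the first model.
- Enter the detrusor and SI-IVC indicators as two terms each: the site's (or surgeon's) achievement rate, and the patient's deviation from that rate. The documentation indicators can stay as planned.
- Report both coefficients for objective 2. Describe the deviation term as open to confounding by indication. Describe the rate term as open to site-level confounding and attenuated by noise in the observed rates, and adjust it for the site factors listed under Secondary Analyses.

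The cost is wording and derived variables from data already collected. The planned single-coefficient model is the special case in which the two coefficients are equal, so nothing is lost. The downside is that the rate coefficient rests on about 172 sites, is imprecise and needs cautious interpretation. Surgeon-level rates would usually be noisier still.
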